### Study procedures

#### Informed consent

Eligible individuals who express interest in participating will receive both verbal and written information about the READ-OUT study. This will include a clear statement that participation is voluntary and that individuals may withdraw at any time without affecting their current or future care, without compromising their legal rights and without needing to provide a reason.

Participants will be given time to review the information and, if they wish, to ask questions, either to the research team, their primary care provider, or to an independent party. After this period, written informed consent will be obtained. This involves the participant signing and dating the consent form, along with the dated signature of the individual who provided the study information and obtained consent. Consent will be taken by a qualified and experienced member of the research team who has been authorised by the chief or principal investigator.

A copy of the signed consent form will be offered to the participant and placed in their medical records where appropriate. The original will be securely stored at the study site. For participants with the mental capacity to consent, participation in the study requires valid informed consent.

READ-OUT will commission professional translation services to meet the needs of specific sites, in different parts of the country. For those unable to write, a witness independent of the study team can provide written evidence of the participant’s verbal consent. Independent consent will be sought at the baseline visit for participation in the READ-OUT substudies, with separate written and verbal information provided with the relevant information.

If an identified potential participant in England, Wales or Northern Ireland lacks capacity to consent to study participation, then advice will be sought from an appropriate consultee in accordance with the Mental Capacity Act (England and Wales 2005, Northern Ireland 2016). The consultee will be asked to sign a written declaration that they understand and accept the role of consultee. If a potential participant lacks the capacity to consent in Scotland, then a Personal Legal Representative will be asked to provide advice to the study team. This can be either a Welfare Guardian/Welfare Attorney or Nearest Relative as set out in the Adults with Incapacity Act (Scotland) 2016. If a participant without mental capacity declines to participate, this expression of wishes will be respected.

#### Baseline visit

The schedule of events for the main READ-OUT study and substudies is set out in figure 2. The baseline study visit may occur on the same day as consent or after an interval if determined by patient choice or local circumstances. 40 mL of blood will be collected from participants via venepuncture prior to processing. Patient demographic information and details of the medical history will be obtained, as well as details of cognitive assessments and biomarker (CSF or PET) testing. Structured assessment will consist of a questionnaire about the participant’s attitude to blood-based biomarker testing for dementia, the EQ-5D-5L (EuroQol 5 Dimensions 5 Levels)^44^ instrument and a Health Resource Use Questionnaire.

**Figure 2 F2:**
[figure not shown]
Schedule of events for the REAl world Dementia OUTcomes observational arm. EQ-5D-5L, EuroQol 5 Dimensions 5 Levels.

#### READ-OUT studies

READ-OUT includes three optional substudies.

Sample test–retest reliability and impact of delays in blood processing. 10% of the full cohort will be recruited to this substudy. Participants invited to this substudy will be invited to attend 1–2 weeks after the baseline visit. 24 mL of blood will be collected by venepuncture with sample processing as set out in the following section.Week 52 visit. This substudy will recruit 20% of the full cohort. Recruited participants will attend at 52 weeks for 20 mL blood sample collection. Participants will be asked to complete the Health Resource Use Questionnaire and the EQ-5D-5L instrument. The aim of the 52-week follow-up substudy is to support the design of the second phase of READ-OUT, including communication of BBM results and understanding biomarker variability, assisting with the estimation of cost-effectiveness and affordability, and determining optimal timing of BBM testing.Self-collection of blood through blood spot card testing. 75 participants will be recruited to this substudy. Participants who consent to take part in this substudy will be asked to provide a blood sample using a dried blood spot card. A prepaid envelope will be provided so the samples can be returned from home after collection. If needed, participants will receive both written instructions and a demonstration on how to collect the blood sample using the provided device.

#### Blood sampling and assay analysis

Blood sampling will be performed after consent. For most patients, 40 mL of blood will be obtained by venepuncture and collected in EDTA and SST tubes. In the main study, samples must be processed within 4 hours, though processing will occur as soon as possible. Samples will be centrifuged to separate plasma and serum at 2000 g for 10 min at 21 °C with no brake. All plasma and serum will be transferred to cryovials in specified volumes. Plasma will be divided into 4×250 µL, 4×500 µL and the remainder into 1 mL tubes. Serum will be divided into 4×250 µL, 2×500 µL and the remainder into 1 mL tubes. They will then be frozen at −80°C prior to transport to the central Biorepository, where they will be held until further analysis.

BBMs will be considered in three tiers:

Tier 1: this tier was set up to include BBMs currently in standard healthcare use, which in 2023 met criteria for phase 3 evidence performance in guidance from the Alzheimer’s Association, the precursor to current Clinical Practice Guidelines.^36^ These tests included phosphorylated tau (p-tau) 181, p-tau 217, neurofilament light chain, AB1-40/42 (with confirmatory testing ≥90% sensitivity and specificity in large and diverse clinical cohorts and/or clinical trials) and apolipoprotein E status.

Tier 2: BBMs were defined by substantial research cohort evidence, falling short of readiness for current healthcare use. These may reflect new assays of beta-amyloid pathology or other processes related to neurodegeneration, its risks or consequences. Assays include glial fibrillar acidic protein, chitinase-3-like protein 1 (YKL-40), progranulin, lipidomics, polygenic risk scores, without specifying the technology used to quantify them (funding restricted the initial phase of tier 2 analysis to Nucleic acid-Linked Immuno-Sandwich Assay Sequencing^45^ (NULISA), but alternative analysis platforms could also qualify for tier 2).

Tier 3: this tier focuses on novel and exploratory biomarkers, with samples retained in the biorepository for use by academic and industry partners. Such biomarkers might be metabolomic, proteomic, transcriptomic, genomic and epigenomic, targeted molecular assays or other biomarkers.

The samples will undergo genotyping using appropriate contemporary methods. Following quantification of extracted cell-free DNA on a Tapestation, whole-genome enzymatic methylation sequencing libraries will be prepared using standard protocols. Sequencing will be performed on the Illumina NovaSeq X+platform at a depth of 30–50× coverage, or a more advanced platform if available at the time of analysis. It is expected that genotyping methodologies may evolve over the course of the study.

Blood samples will be taken for the three subgroups to assess biomarker assay reliability and opportunities for service delivery. To evaluate assay test–retest reliability, participants will have a repeat venepuncture at 1–2 weeks post the baseline visit. At this second visit, four EDTA plasma tubes will be collected. One tube will be kept at room temperature for 2 hours prior to processing, a second tube at 3°C–5°C for 2 hours, a third tube at room temperature for 24 hours, and a fourth tube at 3°C–5°C for 24 hours. Subsequent processing will be as in the main study.

At the 52-week follow-up visit, blood sample processing will mirror the baseline visit.

#### Diagnostic confirmation

The diagnostic ‘ground truth’ will be established through four complementary routes:

Long-term follow-up. Evaluating the consistency of diagnoses over time, acknowledging that diagnostic accuracy improves with extended follow-up.Consensus review. For a subset (10% of READ-OUT, up to 50% per main dementia group), a panel of three experienced clinicians (at consultant, clinical lecturer or senior lecturer level) will review records to provide a consensus clinical diagnosis.Comparison with disease-specific gold-standard tests, including CSF biomarkers for Alzheimer’s, amyloid PET scans and genetic testing for known autosomal dominant causes of common dementias.Neuropathology. Where available, findings from research studies or hospital/coroner neuropathological examinations will be used.

#### Data linkage and corollary data collection

For inclusion in the trial, participants consent to access to electronic health records via data linkage services provided by the NHS or equivalent. Data of interest includes information on therapeutics, inpatient hospital admissions, critical care admissions, attendance at outpatients and coded diagnoses. Following completion of the study, datasets derived from linkage will be held indefinitely if it retains research value to do so and we will seek appropriate ethical approvals to do so following the completion of this study. There is currently no equivalent data linkage service in Northern Ireland, and therefore in this region long-term follow-up will be managed by the local site team.

The READ-OUT dataset will include corollary data from participants where available from other studies. Permission will be obtained from the study participant and study team, examples to date include the Open Network for Frontotemporal dementia Inflammation REsearch, ON-FIRE (chief investigator [name]; variables: BBMs), Quantitative MRI in NHS Memory Clinic, QMIN-MC (chief investigator [name]; variables: structural and functional MRI summary and clinical data), and the Deep and Frequent Phenotyping Study (chief investigator [name]; variables: CSF biomarkers, structural MRI summary and clinical data; neurophysiology).

### Data management and access

#### Participant research results

If a BBM like p-tau 217 is undertaken as part of a clinical healthcare pathway, the clinician can disclose the result as for any other clinical test. The results of the research-only tests will be pseudonymised and not routinely shared with individual participants. As the clinical relevance of the BBM results obtained for research purposes may be uncertain, these results will generally not be communicated to participants. While some BBMs may have an established role in clinical practice in specific scenarios, automatic disclosure of results to participants may have unexpected implications, noting background rates of p-tau 217 positivity in population cohorts.^46^ However, if a site’s clinical principal investigator believes that a specific result could help inform the clinical management of a participant, without directly disclosing the result to them, a request for access to that data may be made. Such requests will be reviewed and considered by the chief investigator or delegate on a case-by-case basis.

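### Blood biomarker results can reach the records that supply two of the four reference diagnoses, and the article states no safeguard

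*Protocol article*

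**What the plan says.** Under Participant research results, the default is restrictive: "The results of the research-only tests will be pseudonymised and not routinely shared with individual participants". Two exceptions follow. A site may request a result if its "clinical principal investigator believes that a specific result could help inform the clinical management of a participant", and "Such requests will be reviewed and considered by the chief investigator or delegate on a case-by-case basis". The second exception covers tests ordered in routine care: "If a BBM like p-tau 217 is undertaken as part of a clinical healthcare pathway, the clinician can disclose the result". Blood sampling and assay analysis lists p-tau 217 among the tier 1 markers that the study evaluates: "These tests included phosphorylated tau (p-tau) 181, p-tau 217, neurofilament light chain".

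Diagnostic confirmation sets four routes to the reference diagnosis. Two depend on clinical records. The first is long-term follow-up: "Evaluating the consistency of diagnoses over time, acknowledging that diagnostic accuracy improves with extended follow-up". The second is a consensus review of 10% of the cohort, in which "a panel of three experienced clinicians (at consultant, clinical lecturer or senior lecturer level) will review records to provide a consensus clinical diagnosis". The other two are disease-specific tests (CSF, amyloid PET, genetics) and neuropathology. The article's list of strengths says that gold-standard confirmation is available only in a subset.

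**The concern.** Each rule is reasonable alone; the difficulty is how they combine. A marker's result may go to the clinician who manages the participant. That clinician's diagnosis may then enter the linked record or the panel's file, and the same marker is later scored against it. This is incorporation bias, also called diagnostic review bias. In Northern Ireland the link is shorter still: Data linkage and corollary data collection gives long-term follow-up to the local site team, and a site's clinical investigator is the person who may request a result.

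The metrics at stake are sensitivity, specificity, predictive values and the area under the ROC curve. They address the question of which markers perform best, contribute to the evidence that the expert panel reviews when it settles BBM choices in year three, and go directly into the economic model. A marker that clinicians can see may gain agreement that an unseen marker does not.

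**Working it through.** **Plan's own figure.** The article gives no figure for exposure or for bias in the reference diagnosis. Its one power statement (N=3165, 17% MCI, OR 1.5 per SD, 80% power) concerns conversion to dementia and is not used here.

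**Does a route exist?**
1. Result to clinician: yes, by approved request or through ordinary clinical testing.
2. Clinician to reference diagnosis: yes for follow-up diagnoses and for the panel, which "will review records to provide a consensus clinical diagnosis". No for CSF, PET, genetics and neuropathology, whose findings do not draw on the blood result.
3. A stated barrier between them: none. The research questions call the case reviewers independent, but an independent reviewer can still read a BBM result in the file. Pseudonymisation and non-disclosure to participants do not shield the clinician's diagnosis.
4. Can exposure be identified later? The Baseline visit section mentions collecting CSF or PET results and does not mention clinically ordered BBMs.

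**How large could the effect be?** Let a share f of reference labels copy the BBM result. The remaining labels are clinical, with sensitivity cSe and specificity cSp, and with errors independent of the BBM given true disease. Assumed, and not in the documents: prevalence π = 0.5 and true BBM sensitivity and specificity Se = Sp = 0.85. Then P(T+) = 0.5×0.85 + 0.5×0.15 = 0.5.

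- a = π·Se·cSe + (1−π)(1−Sp)(1−cSp)
- b = π·cSe + (1−π)(1−cSp)
- Apparent sensitivity = [f·P(T+) + (1−f)·a] / [f·P(T+) + (1−f)·b]; specificity by the mirror-image formula.

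Worked case, clinical label 90%/90% accurate: a = 0.3825 + 0.0075 = 0.39 and b = 0.5. At f = 0 the result is 0.39/0.5 = 0.780. At f = 0.1 it is (0.05 + 0.351)/0.5 = 0.802. At f = 0.2 it is (0.10 + 0.312)/0.5 = 0.824.

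| Clinical label (cSe/cSp) | f = 0 (masked) | f = 10% | f = 20% | Gain at 10% | Gain at 20% |
|---|---|---|---|---|---|
| Error-free, sens. = spec. | 85.0% | 86.5% | 88.0% | 1.5 | 3.0 |
| 90%/90%, sens. = spec. | 78.0% | 80.2% | 82.4% | 2.2 | 4.4 |
| 80%/70%, sensitivity | 65.9% | 69.0% | 72.2% | 3.1 | 6.3 |
| 80%/70%, specificity | 69.4% | 72.8% | 76.1% | 3.4 | 6.6 |

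Gains are in percentage points against the masked value. The range is about 1.5 to 3.4 points at 10% and about 3 to 7 at 20%.

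**Does measured accuracy exceed the truth?** With an error-free label, it does at any f above zero. With a 90%/90% label, 0.78(1−f) + f = 0.85 gives f = 0.07/0.22, about 0.32. With an 80%/70% label, f must be about 0.5 or more.

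**Size of the panel's task.** 10% of 3165 = 316.5, about 317 files.

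**The case against.** The strongest reply is that a condensed article often leaves panel masking and the handling of exposed participants to the full protocol or SAP. That stands as far as it goes: a reader might infer that the panel sees unredacted files and that exposed participants stay in every accuracy analysis, but the article says neither. What remains is more than silence, because the article states both the release rule and the record-based reference, and the two interact.

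Second, release is by exception and needs approval, and clinical p-tau 217 is conditional. The exposed share may be small, and nothing in the text shows that requests will cluster in uncertain cases. This stands, and it is why the sizes above are only illustrative.

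Third, a reader might infer that reported accuracy will exceed true accuracy. The documents do not support that. The Introduction says that clinical assessment can be wrong even at expert centres. With an imperfect label and few exposed participants, measured accuracy stays below the truth. The bias is upward only relative to a masked reference.

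Fourth, two of the four routes give a check that is not circular, although in a subset of unstated size. An unreleased marker that correlates with a released one would also share part of the gain, so the distortion between markers may be smaller than the table suggests.

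**Conclusion.** The point holds as a gap between two stated rules. Index-test results have a permitted path into the records behind two of the four reference routes, and no safeguard is stated. For exposed participants this can raise the visible marker's measured accuracy relative to a masked reference and tilt comparisons towards it. The illustrative size is 1.5 to 3.4 points at a 10% exposed share and 3 to 7 at 20%. It rests on the assumed prevalence and accuracies, on exposed labels following the BBM completely, and on independent errors elsewhere. The true share is unknown. The documents do not establish that accuracy will be inflated above the truth, or that the whole reference standard is circular.

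**What to change.** Keep the release route and make three changes.

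1. Remove BBM results, and mentions of them, from the records given to the consensus panel (about 317 files), and state that the panel is masked to BBM results.
2. Record every research release and every clinical BBM result with its date. When a research release is requested, also record the working diagnosis held at that time. This cannot be left to the analysis plan, because a diagnosis not captured then may not be recoverable, and recruitment is under way.
3. For each marker, report accuracy also with exposed participants excluded or classified by their last diagnosis before exposure, and separately in the subset with CSF, PET or neuropathology.

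The analyses in step 3 should stand beside the main analysis and not replace it. The study relies on diagnoses maturing over follow-up, and setting aside all diagnoses after exposure could make missingness informative. Nor can the study fix a diagnosis in advance of tests ordered in ordinary care; for those, the dated record is what is feasible.

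The cost is a redaction step, a CRF flag and date, a short entry at each release request, and slightly fewer evaluable participants in the added analyses if exposure is uncommon.

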#### Participants confidentiality

The study will adhere to the General Data Protection Regulation (GDPR) and the Data Protection Act 2018, which require the de-identification of data as soon as practicable. The processing of participants’ personal data will be minimised. However, to enable data linkage with participants’ electronic medical records, it will be necessary to collect their full name, date of birth and NHS number. This information will be recorded on the baseline case report form (CRF), with pseudonymised data entered into a secured REDCap database,^47^ with identifiable fields held in a secure database with restricted access.

Each participant will be assigned a unique study identification number, which will be used in all study documents and electronic databases, except for the baseline CRF, where identifying details will be included. All paper records will be securely stored on-site and accessible only to authorised study staff. Limited access to records may be granted to authorised personnel for audit and monitoring purposes. Study staff will take all necessary measures to protect the confidentiality and privacy of participants’ personal data.

#### Data maintenance and access

Personal data collected for electronic health record linkage will be securely stored in a restricted-access database and accessed solely by authorised personnel, and only when necessary to complete NHS data linkage applications. Participant consent will be obtained prior to data collection. Pseudonymised READ-OUT clinical data, recorded during participant visits via CRFs, will be maintained in a separate restricted-access clinical database. Delegated site staff will have access only to their designated data access group, enabling them to enter participant data relevant to their site.

Anonymised READ-OUT data will be held on the DPUK Data Portal, or equivalent trusted research environment in the years ahead. The Data Portal is a secure remote access environment designed for the analysis of cohort data.^48^ A curated, standardised dataset will be made available to eligible researchers through the DPUK Trusted Research Environment (TRE), which forms the core of the DPUK Data Portal. The TRE offers secure, remote access to a wide range of statistical and analytical tools. It supports integration of diverse data types such as medical imaging, proteomics, digital device outputs, genetic data and electronic health records. The standardised dataset will include access to corollary data where participants are recruited to linked DPUK studies.

To protect data confidentiality, only analysis results may be exported; the anonymised READ-OUT dataset itself remains securely within the Data Portal. The TRE applies the highest data security standards (ISO 27001), suitable for NHS data linkage, and supports both anonymised access and advanced analytical methods, including single-site and federated learning.

Access to data is managed through a formal application and review process, with a median turnaround time of 22 days for eligible requests. More details on the access procedure can be found here: DPUK Data Portal.

### Statistical analysis of READ-OUT phase 1

#### BBM modelling and validation

The statistical analysis plan is designed to test the READ-OUT phase 1 research questions with tailored approaches incorporating different tiers of BBMs. Outcomes will be reported in line with relevant standards.^49^

For diagnostic modelling, both traditional statistical approaches (eg, logistic regression) and supervised or unsupervised machine learning techniques (eg, Random Forests,^50^ XGBoost,^51^ support vector machines) will be applied to develop and compare models for diagnostic classification. Performance will be evaluated for individual biomarkers, combinations of biomarkers and models integrating biomarkers with demographic and clinical information, accounting for variation across ethnicity and comorbidities. Diagnostic accuracy will be assessed using metrics such as sensitivity, specificity, positive and negative predictive values, and the area under the receiver operating characteristic curve. The NULISA and other platforms will output high-dimensional data, and we will consider internal validation and biomarker ranking, feature selection, and shrinkage and regularisation methods.

Optimal thresholding of model outputs will be informed by insights from the public and patient involvement and engagement (PPIE) arm of the study, recognising the real-world impact of false positives and false negatives.

Prognostic accuracy will be assessed using longitudinal data and linked electronic health records. Model selection will be guided by the data type and number of time points, and will include approaches such as change-from-baseline analysis of health-related quality of life at 1 year, multilevel and generalised additive models for repeated cognitive outcomes, and models that accommodate censored data for survival and longitudinal diagnostic changes. READ-OUT also leverages DPUK studies with gold-standard biomarker testing, including CSF and PET markers.

In relevant subgroups, we will also evaluate the reliability and resilience of the assays. This includes: (a) assessing deliverability and scalability by comparing standard phlebotomy (all participants) with alternative sampling methods, such as postal blood spot cards; (b) examining test–retest reliability using intraclass correlation coefficients, along with evaluating tolerance to processing delays; and (c) comparing performance across both mass spectrometry and other assay platforms.

